### Sample

Study subjects will be recruited from the observational cohort consisting of all patients assessed at the interdisciplinary outpatient clinic for CPPS at the University Medical Center Hamburg-Eppendorf.

The following criteria will be applied to identify eligible patients in the observational cohort: CPPS diagnosis according to the EAU guidelines [1] and classification of the International Association for the Study of Pain [44], informed consent, sufficient German language skills, age > 18 years, and score ≤ 40 for the mental or physical scale of the 12-Item Short-Form Health Survey (SF-12) [45]. Exclusion criteria are delusional disorders, substance dependence (except nicotine or pain medication), acute suicidal tendencies, planned absences over the treatment period, and current psychotherapy or physiotherapy.

The targeted sample size for the study is 54 participants. Thirty-six participants will be assigned to the intervention group and 18 to the control group. This sample size allows for evaluation of the study in terms of feasibility and can be used to estimate therapeutic effects (pre–post and between groups). Although the sample size is not sufficient to prove the efficacy of the combined treatment programme, the results of the study can be used to calculate the sample size for a subsequent RCT.

Assignment of eligible subjects to treatment and control groups will not be randomized; instead, it will be determined by the ability to regularly participate in the treatment sessions at the University Medical Center Hamburg-Eppendorf. Regular participation is defined as a maximum miss of four of the 18 treatment sessions. The assignment to one of the two treatment sequences (starting with psychotherapy vs starting with physiotherapy) will be randomized.

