
### Data management and analysis

After completion of data collection, raw data will be entered in prepared electronic databases and merged with the electronically captured data. The accuracy of data will be checked by two independent researchers. Data saving and storage will be performed in accordance with the German regulation of Good Clinical Practice [95].

In addition to the quantitative data, feasibility will be analysed using qualitative data, such as answers to open questions in the satisfaction questionnaires and verbal information.

Descriptive statistics will be used to summarize the sample characteristics (e.g. sex, age, and symptom duration) and two-tailed independent *t-*tests will be used to test for significant differences between the intervention and control groups at enrolment (t2).

Subjects will be analysed on an intention-to-treat basis. To examine the course of the symptoms, related variables will be analysed using the pre–post point estimate comparisons, variability estimates, and 95% confidence intervals. The controlled study design allows for within-group as well as between-group comparisons. Paired-sample *t*-tests will be used for within-group comparisons, while the independent *t-*test will be used for between-group comparisons.

The significance level for all *t-*tests will be set at *p* < 0.05.

The analyses of the course of the symptom-related variables will function as estimates of the effect sizes, while effect estimates can be obtained for physiotherapy and psychotherapy separately as well as the overall effect estimates. These estimates can be used to determine the optimal sample size for a subsequent RCT with a normally distributed sample; hence, parametric tests will be applied as statistical procedures in the feasibility study. Factors influencing therapy success will also be examined.

Statistical analyses will be performed with IBM SPSS Statistics, Version 24 (IBM, Armonk, NY, USA).

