Prior studies suggest that physiotherapy is highly valued by patients with CPPS [6, 96] and can empower them to take responsibility for themselves and their coping with pain [97]. During the design of the intervention, the aspect of empowerment and self-management was emphasized, which was a strength of the study. Moreover, instead of adapting a foreign concept such as the Wise–Anderson Protocol [54], a German, already implemented, physiotherapeutic management approach was used. The combination of physiotherapeutic group and individual sessions is not part of the regular health care in ambulatory settings in Germany and might be unexpected for some participants. While they will be in a confidential setting during individual treatments with the physiotherapist, they will have to cope with several other patients being present during performance of exercises. Nevertheless, this group experience can also have a positive effect on the subjects.

We intend to recruit patients from the CPPS outpatient clinic, which has been ongoing since 2012 and serves as the observational cohort in our study design. This cohort is limited in size, and it could be brought into question whether sufficient patients are willing to participate and fulfil eligibility criteria. Their initial assessment at the outpatient clinic might be several months to years prior and their situation with regard, but non-exclusive, to the CPPS might have changed, resulting in non-participation in the study. However, this feasibility study should provide information for further optimization of the treatment approach and power calculation in future RCTs rather than sufficient testing of programme effects. Because of the exploratory nature of the study, no sample calculation was performed, and the selection of controls was based on pragmatic reasons. Nevertheless, to the authors’ knowledge, this study is the first to evaluate a combined programme of psychotherapy and physiotherapy for patients with CPPS while acknowledging the multifactorial aetiology and demand for multimodal therapies [1, 17].

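### p < 0.05 is set for all t-tests without calling them descriptive; between groups and at t2, 36 versus 18 is too few for a non-significant result to inform

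*Protocol article*

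**What the plan says.** The Sample section of the protocol article sets the size: "Thirty-six participants will be assigned to the intervention group and 18 to the control group". It adds that "the sample size is not sufficient to prove the efficacy of the combined treatment programme", and gives the purposes as judging feasibility and estimating effects. The Discussion says that no sample size calculation was done and that the study should inform optimisation of the treatment and "power calculation in future RCTs rather than sufficient testing of programme effects".

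The Data management and analysis section plans three kinds of t-test:
- two-tailed independent tests that "will be used to test for significant differences between the intervention and control groups at enrolment (t2");
- paired tests within groups;
- independent tests between groups.

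One rule covers them: "The significance level for all" t-tests is set at p < 0.05. The same section plans point estimates, variability estimates and 95% confidence intervals for the course of symptoms, and says the effect estimates can be used to size a later RCT. It plans no estimate or interval for the t2 comparison. Assignment to intervention or control is not randomised (Sample; Control group), and the Discussion acknowledges possible selection bias.

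**The concern.** A significance threshold invites a verdict on each outcome, yet the article says the study is not sized to give one. Nothing in the analysis section marks the p-values as descriptive.

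Two things are at stake. First, the secondary aim is to obtain preliminary indicators of efficacy and effect sizes for a later trial. If between-group results came to be read as significant or not, real moderate effects would often be set aside, and those that passed would be too large on average. Second, the groups are formed by who can attend, so readers need the size of any difference at enrolment. A test with low power cannot supply it, and a non-significant result is easily taken for comparability.

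**Working it through.** The article states no power, effect size or SD, so there is no figure of its own to reproduce. True differences are assumed values in SD units.

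**Inputs.** n = 36 and 18 (Sample). Alpha = 0.05 (Data management and analysis). Two-sided testing is stated for the t2 comparison and assumed for the other tests. Equal SDs, independent observations and no drop-out are also assumed.

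**Independent t-test, 36 versus 18**
- Standard error of the difference: √(1/36 + 1/18) = 0.289 SD.
- Critical value on 36 + 18 − 2 = 52 degrees of freedom: 2.007.
- Smallest significant observed difference: 2.007 × 0.289 = 0.58 SD. This is also the approximate half-width of the 95% interval.
- Power from the non-central t distribution with noncentrality d/0.289:

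| True difference (SD, assumed) | Power |
|---|---|
| 0.2 | 10% |
| 0.3 | 17% |
| 0.5 | 40% |
| 0.8 | 78% |

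- 80% power needs a true difference of 0.82 SD.
- Drop-out lowers these figures. Power at 0.5 SD is 34% with an assumed 15% loss (31 versus 15) and 32% with an assumed 20% loss (29 versus 14, threshold 0.66 SD).

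**Exaggeration if results are picked on significance.** In simulated trials at 36 versus 18, the mean absolute standardised difference among significant results was 0.74 when the truth was 0.3 and 0.80 when it was 0.5. The ratios are 0.74/0.3 ≈ 2.5 and 0.80/0.5 = 1.6. Scaled by the true rather than the observed SD they are 2.4 and 1.5. As an illustration of the consequence, take n per arm = 2 × (1.96 + 0.84)²/d², for 80% power at 1:1. Sizing on 0.80 SD gives about 25 per arm, whereas a true 0.5 SD needs about 63.

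**t2 comparison.** The same test and group sizes apply. A true imbalance of 0.5 SD is missed with probability 1 − 0.40 = 0.60. An observed imbalance of exactly 0.5 SD would be non-significant, because 0.5 < 0.58, yet its interval would be about 0.5 ± 0.58, that is −0.08 to 1.08 SD. Such a result leaves a large imbalance possible.

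**Paired t-test.** For the 36 intervention patients at a standardised change of 0.5, the noncentrality is 0.5 × √36 = 3.0 and power is about 83%. The threshold is about 2.03/6 = 0.34 SD of change. For the 18 controls, power at the same change is about 52%.

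**The case against.** A reader might infer that the plan contradicts itself, that p < 0.05 works as a decision rule, and that every t-test is underpowered. The document does not support that reading.

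- Disclaiming proof and sufficient testing is not the same as saying that no test will be run. The article calls the study exploratory and speaks of preliminary indicators. This is a tension, not a strict contradiction.
- No go/no-go decision, efficacy claim or choice of outcome is tied to a p-value. The exaggeration figures apply only if outcomes are selected on significance, which the plan nowhere says it will do.
- The low-power argument covers the independent tests. It does not cover the paired test in the intervention group, where the limitation is the lack of a control rather than power.
- A 95% interval for a difference that excludes zero is the same event as p < 0.05, so dropping the threshold removes no information where intervals are already planned.
- Comparing non-randomised groups at baseline is reasonable, and selection bias is openly acknowledged.

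All of this stands, and it limits the point. It does not remove it. The threshold is stated and unqualified, so the concern is a choice the article makes, not a detail left to another document. At t2 the argument that intervals are already planned does not apply, because only the test is planned there.

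**Conclusion.** The point holds in limited form. The between-group tests at 36 versus 18 say little when non-significant: power is about 17% at 0.3 SD and 40% at 0.5 SD, and an observed difference above 0.58 SD is needed. The t2 test cannot show comparability, since it misses a true 0.5 SD imbalance about 60% of the time. The t2 comparison is the stronger half, because no estimate accompanies the test there.

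The figures rest on the assumed effect sizes, equal SDs, independent observations and full retention; drop-out makes them worse. The conclusion holds for any true difference below about 0.8 SD. That outcomes will be sorted by significance, or that t2 non-significance will be reported as comparability, are foreseeable uses and not stated ones. The primary feasibility outcome is untouched. The change is worth making because it improves what the secondary results can support at almost no cost.

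**What to change.** In Data management and analysis:
1. Replace the t2 significance tests by standardised differences between the groups with 95% confidence intervals.
2. Make the already planned point estimates and 95% confidence intervals the main result for the secondary outcomes. Drop the p < 0.05 criterion, or label all p-values as descriptive.
3. State that neither significance nor non-significance will be used to claim efficacy or lack of effect, or to choose which outcomes or effect sizes feed the later RCT sample size.

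This needs no new data or patients. The only added output is the t2 differences with their intervals. The downside is that the report can no longer present a result as a significant effect.

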**Methods:**

A feasibility study with a crossover design based on the principles of a ‘cohort multiple randomized controlled trial’ will be conducted to test a combined therapy for patients with CPPS. The study will consist of two consecutive treatment modules (cognitive behavioural group psychotherapy and physiotherapy as individual and group sessions), which will be applied in varying order. The modules will consist of nine weekly sessions with a 4-week break between the modules. The control group will undergo treatment as usual. Study subjects will be recruited from the interdisciplinary outpatient clinic for CPPS at the University Medical Center Hamburg-Eppendorf. Thirty-six patients will be assigned to the intervention, and 18 patients will be assigned to the control group. The treatment groups will be gender homogeneous. Feasibility as the primary outcome will be analysed in terms of the demand, acceptability, and practicality. Secondary study outcomes will be measured using validated self-rating-scales and physical examinations.

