### Intervention group

The intervention will consist of two consecutive treatment modules (cognitive behavioural group psychotherapy and physiotherapy as both group and individual sessions). A 4-week break is scheduled between the two modules. The intervention group has two branches; therefore, subjects will start with either one of the modules described in the following. A group size of nine patients for the psychotherapy as well as for the physiotherapy group sessions is regarded as adequate even in the event of drop-outs. This group size also reflects the maximal number of patients allowed in a CBT group in the German healthcare system [47]. The groups will be gender homogeneous because CPPS is characterized by symptoms in an intimate body region potentially associated with shame [48]. With a targeted sample size of 36 participants in the intervention and a group size of nine in the therapeutic sessions, the overall intervention group will consist of four therapeutic groups, two with only male participants and two with only female participants. One group of each gender will start with either psychotherapy or physiotherapy, resulting in four treatment groups in the intervention group.

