### Control group

Allocation to the control group will not be randomized; instead, this will be determined by the ability to participate in the intervention occurring at the University Medical Center Hamburg-Eppendorf. It was considered difficult for patients outside the greater Hamburg area to participate; therefore, they will be allocated to the control group. The control group will not receive any specific intervention as part of the study; nonetheless, patients can seek treatment as usual from their local healthcare provider. Assessment of the control group will be done at two time points; first, at time point t2, which is the enrolment time; and second, at time point t7, which is 4 weeks after the intervention group has finished the second intervention module. The results of these measurements will be compared with the results of the intervention group to gather initial insight into the efficacy of the intervention compared to treatment as usual.

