The group assignment will be based on the ability of regular participation in the intervention which might lead to selection bias. However, we deemed regular attendance important for the positive effect of the whole intervention programme, and as the complete intervention will last 22 weeks (each intervention module has a duration of 9 weeks with a 4-week break in between) it will require a great concession in terms of time. Participants will not only have a weekly appointment at University Medical Center Hamburg-Eppendorf, they will also have to prepare the psychotherapeutic sessions by reading the workbook chapters and completing the respective questionnaires. It is unclear whether patients will comply with these requirements so that they will be prepared enough to follow and understand the content of the single psychotherapeutic sessions. Moreover, it is expected that at least some subjects will miss one or more sessions due to shift work, unplanned vacations, or other reasons. This might result in difficulties in understanding the content of the subsequent sessions, influencing the effect of the intervention. However, the subjects will have manuals for both the psychotherapy and physiotherapy components, which will allow them to educate themselves even if they have missed a session. Both intervention modules will be applied in a subsequent order rather than to deliver physiotherapy and psychotherapy at the same time. This approach was chosen so that participants have to make time for a weekly appointment and estimate the effects of each module separately. Nonetheless, some patients might find it tempting to select the intervention module they find more interesting or suitable for their individual situation and skip the other one. In addition, the subsequent order contributes to the prolongation of the overall treatment period. All psychotherapy sessions will be provided as group treatments. Group sessions will be accompanied by a workbook, which requires that participants adhere to specific assignments and may influence their motivation. Nonetheless, the workbook provides support and advice both during the intervention period and after its completion.

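### Per-module pre–post changes are uncontrolled, so they do not give the separate physiotherapy and psychotherapy effects that the article says can be obtained and used to size an RCT

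*Protocol article*

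**What the plan says.** The Abstract (Methods) describes "A feasibility study with a crossover design". All 36 intervention patients receive both modules, and their order is randomised (Sample). "A 4-week break is scheduled between the two modules" (Intervention group). Measurements fall at the start and end of the first module (t3, t4), at the start and end of the second (t5, t6), and four weeks later at t7 (Procedure).

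For the comparison group, "Assessment of the control group will be done at two time points": t2 and t7. Its allocation is not randomised and depends on being able to attend (Control group).

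On analysis, Data management and analysis says "The controlled study design allows for within-group as well as between-group comparisons". It continues that "Paired-sample *t*-tests will be used for within-group comparisons" and gives the independent t-test for between-group comparisons; "The significance level for all *t-*tests will be set at *p* < 0.05". It then states that "effect estimates can be obtained for physiotherapy and psychotherapy separately as well as the overall effect estimates", and that the estimates can be used to find the sample size of a later RCT. The Discussion gives the wish to "estimate the effects of each module separately" as one reason for running the modules one after the other.

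**The concern.** The article credits the design with a property that it lacks. A separate effect for a module requires knowing how the same patients would have changed over those nine weeks without it. No control is measured at t3, t4, t5 or t6, so no untreated comparison covers either module window. An analysis plan that is not shown could not supply those measurements.

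At stake is a declared use of the results. If uncontrolled change is read as module effect, the effect size carried into the next trial's sample size calculation is wrong by an unknown amount. The one comparison of the modules that randomisation protects, between sequences in the first period, is not specified as the module estimate.

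**Working it through.** The article gives no power calculation, SD or expected change, so there is no stated figure to reproduce. Its counts are consistent: 4 groups × 9 = 36; 36 + 18 = 54; 9 + 4 + 9 = 22 weeks. Two sequences give 18 patients each.

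**What each change contains.** Let s1 to s5 be the mean changes without treatment over t2–t3, t3–t4, t4–t5, t5–t6 and t6–t7. Let C and P be the psychotherapy and physiotherapy effects. Let c and p be the net extra change during the second module that is due to having had psychotherapy or physiotherapy first.

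- Psychotherapy first: t3–t4 = C + s2; t5–t6 = P + s4 + c
- Physiotherapy first: t3–t4 = P + s2; t5–t6 = C + s4 + p
- Controls: t2–t7 = s1 + s2 + s3 + s4 + s5

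A first-module gain that stays stable is present at both t5 and t6 and cancels. Only its growth, decay or interaction enters c or p. First-module changes contain no carryover, but they still contain s2.

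**Can C and P be separated?**

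- Allowing carryover: add any k to C and P, subtract k from s2, add k to s4, and subtract 2k from c and p. Every line above is unchanged, so the data cannot fix C or P (rank 8 of 9). Only C − P is determined, from the first period.
- Intervention data alone, no carryover: again only C − P (rank 6 of 7).
- Controls added, assuming no carryover, additivity and parallel trends: the programme-minus-control change over t2–t7 gives C + P, the first period gives C − P, and both effects follow (rank 7 of 7). The planned paired t-tests do not do this.

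**What the error could do (assumed values; the article gives none).**

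- True effect −0.30 SD with secular change −0.20 SD: the first-module change is −0.50 SD. With c = p = −0.10 or −0.20 SD, pooling both positions gives ½(−0.50) + ½(−0.60) = −0.55 SD or ½(−0.50) + ½(−0.70) = −0.60 SD. If patients instead worsened by 0.20 SD, the first-module change would be −0.10 SD, an understatement.
- No module effect, secular change s, pre–post correlation 0.6: the noncentrality is s/√(2(1 − 0.6)) × √n. At n = 36, s = 0.2 gives 1.34 and s = 0.4 gives 2.68. The paired test is then significant (two-sided 0.05) in 26% and 74% of trials. At n = 18 the figures are 15% and 43%.
- RCT size per arm (80% power, two-sided 0.05): 175 at d = 0.3, 63 at d = 0.5, 44 at d = 0.6.

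**Precision of the randomised first-period contrast.** At 18 vs 18, SE = √(2/18) = 0.333 SD and t(34) = 2.032, so the half-width is 0.68 SD. Adjusting for t3 multiplies this by √(1 − r²): 0.59 SD at r = 0.5 and 0.48 SD at r = 0.7 (assumed correlations). Power is 32% at d = 0.5 and 67% at d = 0.8. All of this treats patients as independent. With groups of nine and intracluster correlation ρ, the half-width grows by about √(1 + 8ρ). With one group per sex per sequence, group and sequence are also hard to separate.

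**The case against.** The strongest reply is that feasibility is the primary aim. The article calls its efficacy findings preliminary, says the sample cannot prove efficacy, and admits possible selection bias. No primary conclusion rests on the module estimates. This stands and limits the weight of the point. It does not answer it, because the article nowhere says that the per-module estimates are uncontrolled and it names RCT sizing as their use.

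Several stronger readings are tempting, and the documents do not support them:

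- **The estimates are inflated.** Spontaneous improvement would inflate them. Natural worsening, decay of the first module's gain or a floor effect would shrink them. Regression to the mean from the SF-12 entry threshold may largely precede t3, because t1 can lie months or years earlier.
- **Lasting skills make the four-week break fatal.** A workbook meant to help after completion makes persistence plausible, but a stable gain cancels in t5–t6.
- **The randomised comparison is discarded.** Study design says that both sequences will be tested, and the between-group t-test is not expressly limited to intervention versus control. The sequence contrast is unspecified, not excluded.
- **Module effects are claimed against no treatment.** The article makes no such claim, and its treatment-as-usual comparison is already confined to t2 and t7.
- **Separate effects can never be identified.** They can, under the strong assumptions set out in the working.

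The intervals t2–t3 and t4–t5 contain no module sessions and offer a rough within-patient guide to secular change. The second may carry the first module's effect, and neither need match the change during a module.

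**Conclusion.** The concern holds for the analysis as described. A paired change over a module is an uncontrolled change and does not isolate that module's effect, and the controls cannot correct it on the present schedule. Separate effects would need no carryover, additivity, and parallel trends with a control group chosen by ability to attend. The planned t-tests use none of these.

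Neither the direction nor the size of the bias can be derived from the article. The figures of 0.5 to 0.6 SD for a true 0.3 SD, and 44 to 63 instead of 175 patients per arm, show what modest assumed secular change and carryover would do. They are not predictions. What the design does support is the difference between modules in the first period, with a half-width of about 0.68 SD before clustering, and a non-randomised comparison of the whole programme with treatment as usual. The point concerns secondary, exploratory estimates and leaves the feasibility aim untouched.

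**What to change.** 1. Withdraw the statement in Data management and analysis that separate module effects are obtained, and align the matching reason in the Discussion. Do not size an RCT from per-module pre–post changes.
2. Report t3–t4 and t5–t6 changes as uncontrolled within-group change, by sequence and by position (given first or second), without pooling the two periods.
3. Specify the first-period randomised contrast as the psychotherapy-versus-physiotherapy estimate: t4 score by sequence, adjusted for t3 and sex. Do not also adjust for wave where sex and wave coincide. Even where they do not, intercept, sequence, sex and wave would use up all four means of the four planned groups. Trial status mentions a further pair of groups, so set the adjustment by the groups actually run.
4. State that this contrast is relative, exploratory and imprecise, and give its interval with the clustering caveat.
5. State that only the whole programme (t2–t7) is compared with treatment as usual, and that this comparison is not randomised.

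The cost is wording and one specified analysis on data already scheduled. The price is a narrower claim: a relative, imprecise module contrast in place of two module effects. Measuring controls at t3–t6 as well would make C and P estimable under additivity and parallel trends (rank 13 of 13 with carryover terms). That needs new data, comes too late for the groups already treated, and would still rest on a non-randomised control.

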### Objectives

Regarding the advocacy for multimodal therapy established in the guidelines of the European Association of Urology (EAU) [1], there is an urgent need to examine combined interventions for patients with CPPS. However, due to constraints of resources, not all interventions can be tested for efficacy and effectiveness. In this case, a feasibility study can be used to decide whether a treatment method is worth further investigation and whether changes should be applied to the intervention [42].

Therefore, the primary aim of this study is to explore the feasibility of a combined psychotherapeutic and physiotherapeutic treatment for both female and male patients with CPPS. The results from this study will be used to generate an enhanced therapeutic approach, which might be subject to further testing. Additionally, the secondary objective of this study is to determine the preliminary indicators for the efficacy of this treatment programme regarding urological symptoms, psychological and physical correlates, health-related quality of life, and healthcare utilization. The results can be used to calculate the optimal sample size for a randomized controlled trial (RCT).

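### The observed effect sizes cannot determine an optimal sample size for a later RCT: at 36 versus 18 non-randomized patients they are too imprecise and open to bias

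*Protocol article*

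**What the plan says.** The key text is in the protocol article, Data management and analysis. It first says what is estimated: "The analyses of the course of the symptom-related variables will function as estimates of the effect sizes". It adds that estimates can be had for physiotherapy and psychotherapy separately and overall. It then gives their use: "These estimates can be used to determine the optimal sample size for a subsequent RCT with a normally distributed sample". The same sentence goes on to justify parametric tests on that ground.

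Three other places mention the use more loosely, without naming effect sizes:
- Objectives: "The results can be used to calculate the optimal sample size for a randomized controlled trial (RCT".
- Sample: "the results of the study can be used to calculate the sample size for a subsequent RCT".
- Discussion: "this feasibility study should provide information for further optimization of the treatment approach and power calculation in future RCTs".

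On the design, the Sample section says "The targeted sample size for the study is 54 participants" and "Thirty-six participants will be assigned to the intervention group and 18 to the control group". It also says "Assignment of eligible subjects to treatment and control groups will not be randomized; instead, it will be determined by the ability to regularly participate"; only the order of the two modules is randomized. The Control group section sends patients from outside greater Hamburg to the control group and assesses controls at t2 and t7 only. Between-group comparisons use an independent t-test, and no adjustment is named.

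**The concern.** Sample size depends on the inverse square of the target difference, so an error in the planning effect is magnified in the size of the next trial. An estimate that is too high by chance or through bias gives an RCT that is too small. An estimate that is too low gives an impractically large one, or suggests that the treatment should be dropped. Calling the resulting figure optimal claims a precision and freedom from bias that 54 non-randomized patients cannot provide. The cost would fall on the later RCT and its participants, not on the present study.

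**Working it through.** The article gives no effect size, standard deviation or power, and says that no sample size calculation was done. There is therefore no figure to reproduce. The question is what an effect estimate from this design can carry.

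**Inputs from the article:** 36 intervention and 18 control patients; no randomization between them; significance level 0.05.

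**Assumptions not in the article:** RCT with 80% power, 1:1 allocation and a two-sided test; true or observed d between 0.3 and 0.8; no drop-out unless stated.

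**1. Precision of the between-group estimate.** SE(d) = √(1/36 + 1/18 + d²/(2×54)). At d = 0.5 this is √(0.0278 + 0.0556 + 0.0023) = 0.293. The 95% CI is 0.5 ± 1.96 × 0.293 = -0.07 to 1.07. The exact noncentral-t interval is -0.08 to 1.07.

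**2. Implied RCT size.** n per arm = 2(1.96 + 0.84)²/d².
- At 0.5: 62.8, so 63, or 64 with the t correction.
- At 1.07: 13.7, so 14, or 15 with the t correction.
- At the lower limit there is no finite n, because the interval includes zero.

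Other observed values, with exact intervals and the normal formula:

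| Observed d | 95% CI | n per arm at estimate | n per arm over the CI |
|---|---|---|---|
| 0.3 | -0.27 to 0.87 | 175 | 21 to no finite value |
| 0.8 | 0.21 to 1.38 | 25 | 9 to 356 |

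With 20% drop-out (29 versus 14), the interval at d = 0.5 widens to -0.15 to 1.14. Clustering within therapy groups of nine widens it further. With an assumed ICC of 0.05 to 0.10, the base SE √((1 + 8×ICC)/36 + 1/18) rises from 0.289 to 0.307–0.325.

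**3. Real power of an RCT sized on the observed d.** Such an RCT has less than 80% power when observed d exceeds true d. It has less than 50% power when observed d exceeds true d × 2.80/1.96 = 1.43 × true d. Among positive estimates, with no bias, the normal approximation gives:

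| True d | P(observed d > 0) | Below 80% power | Below 50% power |
|---|---|---|---|
| 0.4 | 0.917 | 0.5/0.917 = 55% | P(d > 0.572) = 0.278; /0.917 = 30% |
| 0.5 | 0.958 | 0.5/0.958 = 52% | P(d > 0.715) = 0.232; /0.958 = 24% |
| 0.8 | 0.997 | 0.5/0.997 = 50% | P(d > 1.143) = 0.125; /0.997 = 13% |

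Simulation gives about 48–56% and 11–31% over the same range, depending on how n is rounded and whether estimates barely above zero are counted. At true d = 0.5, the derived n per arm has a 10th to 90th percentile of 20 to 458, against a correct value of 63.

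**4. Confounding.** More patients would not remove this. If allocation by residence and ability to attend adds an assumed +0.2 SD at true d = 0.5, then 76% of the derived RCTs fall below 80% power and 48% below 50%. With -0.2 SD, the median n per arm is 124 and 15% of studies show no benefit. The article gives no basis for the sign or size of this bias.

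**5. Pre–post and module estimates.** The 95% half-width is t(35)/√36 = 2.03/6 = 0.34 SD of the change score for all 36, and t(17)/√18 = 2.11/4.24 = 0.50 for one sequence of 18. Bias is the larger problem. Module effects are read over t3–t4 and t5–t6, when no control is measured. They mix treatment with natural course and regression to the mean and, in the second module, with carry-over from the first.

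**6. What the study can supply.** The pooled SD on 52 df has a 95% CI of 0.84 to 1.24 times its estimate. With a target difference fixed in advance, n would vary only by 0.84² = 0.70 to 1.24² ≈ 1.53 times. The upper one-sided 80% limit of the SD is √(52/χ²₀.₂₀(52)) = 1.096 times the estimate.

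**The case against.** The strongest reply is that the wording is permissive. The article says that the estimates can be used, not that the point estimate alone will set the RCT's size. It also plans variability estimates and 95% confidence intervals, says the sample cannot prove efficacy, concedes possible selection bias and calls the study exploratory. Any later RCT would need its own justification of sample size.

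Much of this stands. A reader might infer that the article commits the RCT to the observed effect; it does not. A reader might also infer that four sections tie effect sizes to sample size. Only Data management and analysis does so. The statements in Objectives, Sample and Discussion are compatible with using standard deviations, attrition and uptake.

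Nor should one infer that the RCT would go ahead only after a significant result, so that its size would always be too small. The article sets no such gate, and the derived size can err in either direction.

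What does not stand is that the caveats settle the matter. The Sample section disclaims proof of efficacy and endorses the sample-size use in the same sentence. Nowhere does the article say how an interval that includes zero would be turned into a sample size. Observed effect sizes are the only sizing input it names, and it calls the result optimal.

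**Conclusion.** The point holds for the statement in Data management and analysis. The design does not have the property claimed there. At an observed d of 0.5, the implied RCT ranges from about 15 per arm to no finite size. For a true d of 0.4 to 0.8, roughly half of positive estimates would lead to an RCT with less than 80% real power, and about 11–31% to one with less than 50%. These figures assume 80% nominal power, no drop-out, no clustering and no bias. Drop-out and clustering make the estimate less precise, and confounding could shift it either way.

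Severity is moderate. The flaw concerns the stated use of the secondary analysis. It does not invalidate the feasibility aim or change any test or estimate in this study, and the article gives no ground for a graver reading.

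**What to change.** In Data management and analysis, drop the word optimal and state three things:
1. Observed effects, overall and by module, are reported descriptively with 95% confidence intervals and will not set the RCT's target difference.
2. That difference will be a minimally important difference on the outcome chosen for the RCT, fixed independently of this study's results.
3. This study supplies only the outcome SD, the t2–t7 correlation, attrition and uptake. The SD should be taken at a conservative upper limit, for example about 1.10 times the pooled SD if all 54 are analysed. With 29 versus 14 (41 df), the same formula gives 1.11.

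For the therapy-group ICC, use an assumed range and not this study's estimate. The Intervention group section plans four groups, one for each combination of gender and sequence, so variation between groups cannot be separated from those two factors.

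The sentences in Objectives, Sample and Discussion need only be aligned with this wording. The change costs no patients, visits or analyses. Its one drawback is that the future RCT may look larger than an optimistic estimate from this study would suggest.
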